## Abstract

Background

Down syndrome (DS) is one of the most common chromosomal anomalies, affecting a substantial number of newborns globally. Pediatric patients with DS face a range of health challenges, including complex and often underrecognized pain experiences. These children may exhibit atypical responses to pain, such as reduced verbal expression, behavioral changes (e.g., freezing), or lower pain thresholds, that can render conventional pain assessment strategies insufficient. Consequently, there is a critical need for multidimensional tools specifically tailored to the characteristics of this vulnerable population. This study aims to develop and validate a novel mixed-methods instrument - the ANDREAS tool - designed to accurately assess acute pain in children with DS by integrating behavioral observations with self-report measures, where feasible.

Methods

A mixed-methods approach will be employed to adapt a pain assessment scale suitable for children with DS, combining behavioral observations with self-reported measures when possible. Pain-related behaviors will be identified through an extensive literature review and focus group discussions involving researchers, parents, and healthcare professionals. Additional methodological components will include defined randomization procedures for participant selection, clear inclusion and exclusion criteria, a standardized venipuncture protocol to induce pain, and a tailored training program for assessors to ensure methodological rigor. The resulting instrument, ANDREAS, will undergo validation using exploratory factor analysis and internal consistency testing (Cronbach’s alpha).

Results

The study is expected to yield a validated tool capable of capturing both the presence and severity of acute pain in pediatric patients with DS. Key behavioral indicators, such as freezing, defined as the absence of movement for at least five seconds during a painful stimulus, will be operationalized and assessed using a structured 0-4 rating scale. The integration of behavioral and self-report data is anticipated to enhance the sensitivity and specificity of pain detection in this population.

Conclusions

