Each study phase involves specific procedures and participant groups, selected according to the phase’s objectives. Inclusion and exclusion criteria will be defined separately for the qualitative and quantitative components. The expected study duration is approximately 18 months, covering recruitment, data collection, and validation.

Qualitative study sample

The qualitative sample will consist of approximately 30 parents of children and adolescents with DS, chosen to reflect a range of ages and comorbidities while maintaining comparable levels of cognitive impairment. This sample size is based on evidence that 99.3% of concepts, themes, and content typically emerge after about 30 interviews [15]. Recruitment will continue until data saturation is reached [16].

Inclusion criteria include parents of children or adolescents with DS who present with mild to moderate-severe cognitive impairment, regardless of clinical condition. Participants must provide written informed consent and agree to participate in focus groups.

Exclusion criteria include parents who are unable to actively participate due to medical or psychological conditions, those whose children do not consent to the study, or those whose children’s cognitive impairments and pain-related behaviors are too complex to assess reliably.

Quantitative study sample and eligibility criteria

The sample size for the observational study is based on a hypothesized prevalence of pain in the pediatric DS population of approximately 30% [10], with a 95% confidence level and a margin of error of 7%. The standard formula for estimating sample size in prevalence studies is as follows:

\[n = \frac{Z^2 \cdot p \cdot (1 - p)}{d^2},\]

where Z = 1.96 (for 95% confidence), p = 0.30, and d = 0.07.

The resulting estimated sample size is approximately 165 child participants. All pediatric subjects whose parents provide informed consent will be eligible for inclusion.

Inclusion Criteria

Eligible participants will be children older than eight years whose parents voluntarily agree to enroll them in the study. This cohort will include children whose parents participate in the initial focus group as well as those involved in testing the newly developed pain assessment tool. Instrument testing will take place in healthcare facilities during venipuncture procedures in order to evaluate the tool’s capacity to detect the presence and intensity of pain.

Exclusion Criteria

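### The sample size of 165 children rests on the precision of a population pain prevalence that no objective or planned analysis estimates, so the stated margin says nothing about the validation

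*Protocol article*

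**What the plan says.** Under Quantitative study sample and eligibility criteria (Materials and methods), the Protocol article states: "The sample size for the observational study is based on a hypothesized prevalence of pain in the pediatric DS population of approximately 30" per cent, "with a 95% confidence level and a margin of error of 7" per cent. It introduces the calculation with "The standard formula for estimating sample size in prevalence studies is as follows", gives the inputs as "where Z = 1.96 (for 95% confidence), p = 0.30, and d = 0.07", and concludes: "The resulting estimated sample size is approximately 165 child participants". No other basis for the number is given.

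The quantity being sized for is therefore a single proportion. The rest of the article has a different target:

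- **Study objectives:** the primary objective is to design and validate the instrument. The secondary objective is to identify pain behaviors by degree of intellectual disability.
- **Study procedures, fourth phase:** the observational study is to assess face, content and construct validity, using EFA, and reliability.
- **Statistical analysis:** descriptive statistics; EFA after sampling-adequacy and sphericity checks, with loadings of at least 0.40 acceptable; and Cronbach's alpha, with 0.70 or more taken as satisfactory.
- **Inclusion Criteria:** "Instrument testing will take place in healthcare facilities during venipuncture procedures".

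On how children enter the sample, the abstract lists "defined randomization procedures for participant selection" among the methodological components. The sample-size section says: "All pediatric subjects whose parents provide informed consent will be eligible for inclusion".

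**The concern.** A sample size with a stated confidence level and margin tells the reader how precisely the study will answer its question. Here the margin belongs to a population prevalence, and the study's question is whether an instrument is valid and reliable. Someone reading 95% confidence and 7 points would reasonably assume that the validation had been sized to that standard. It has not: no part of the article connects 165 to EFA or to alpha.

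Nor could the design deliver the prevalence if it were wanted. The 30% is a hypothesized figure for the pediatric Down syndrome population. The tool is tested while children undergo a needle procedure, at one center, in families who have agreed to take part. The share of such children who show pain is a procedural figure in a volunteer sample, not that prevalence.

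What is at stake is how the result is read. The article expects the instrument to be used in clinics and at home. An alpha close to the 0.70 benchmark would be called satisfactory, and the only precision statement in the plan would give no idea of how uncertain that alpha is.

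**Working it through.** **1. The plan's own figure.** Inputs from the sample-size section: Z = 1.96, p = 0.30, d = 0.07.

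n = Z² p(1 − p) / d² = 3.8416 × 0.21 / 0.0049 = 164.64, rounded up to 165.

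Half-width at n = 165: 1.96 × √(0.21 / 165) = 0.0699, or 7.0 points. The stated figure reproduces. The fault is in what is being estimated, not in the arithmetic.

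**2. Is that proportion estimated anywhere?**

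| Place in the article | Target | Population prevalence? |
|---|---|---|
| Primary objective | Design and validation of the tool | No |
| Secondary objective | Behaviors by degree of disability | No |
| Fourth phase | Validity (EFA) and reliability | No |
| Statistical analysis, descriptives | Proportions, pain intensity and other summaries | Not named; see the objection |
| Statistical analysis, validation | EFA, Cronbach's alpha | No |

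**3. What 165 gives for Cronbach's alpha.** Feldt's interval for an observed alpha a, with n children and k items, has the limits

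lower = 1 − (1 − a) F(0.975), upper = 1 − (1 − a) F(0.025),

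where F(q) is the q quantile of the F distribution on n − 1 and (n − 1)(k − 1) degrees of freedom. The final item count is not in the article, so k is an assumption and a range is shown. With a = 0.70 (the plan's benchmark) and n = 165:

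| Items k (assumed) | Degrees of freedom | F(0.975) | F(0.025) | 95% CI |
|---|---|---|---|---|
| 5 | 164, 656 | 1.263 | 0.778 | 0.62 to 0.77 |
| 12 | 164, 1804 | 1.241 | 0.789 | 0.63 to 0.76 |
| 30 | 164, 4756 | 1.233 | 0.793 | 0.63 to 0.76 |

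For k = 12: 1 − 0.30 × 1.241 = 0.628 and 1 − 0.30 × 0.789 = 0.763. The interval hardly depends on k.

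**4. What 165 gives for EFA.** Children per item: 165 / 12 = 13.75; 165 / 20 = 8.25; 165 / 30 = 5.5. The value 12 is only the number of candidate behaviors in the second phase. The list is settled in the fourth phase, so the ratio that will apply is not yet known. Unlike the alpha interval, it depends strongly on the item count.

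**The case against.** The strongest reply is that the number itself is not shown to be wrong. At about 12 items, 165 gives nearly 14 children per item and a fairly tight interval for alpha, and nobody would need to be added. This stands. A reader might infer that the study is underpowered or too small, but the article fixes neither an item count nor a target precision against which 165 could fail.

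A second reply is that the descriptive statistics include proportions and summaries of pain intensity, so a share of children with pain may well be reported. This also stands, and it rules out saying that the margin could apply to nothing the study reports. It does not rescue the rationale: such a share would be incidental, and would not be the population prevalence for which the 30% was assumed.

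A third reply concerns selection. A reader might infer that the abstract's randomization claim is flatly contradicted because every child with parental consent is enrolled. The text says that such children are eligible, the age criterion and the exclusion for profound impairment also apply, and eligibility does not rule out random selection among those eligible. The full protocol may describe the procedure. What remains is that the article names randomized selection in the abstract while its own sampling text mentions only consent and eligibility, and the two need to be reconciled.

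Finally, a reader might want the 165 judged on inter-rater agreement or on correlations with other measures. The article places Cohen's kappa in pilot testing and lists correlation coefficients only among the descriptives, so neither is a planned analysis that 165 has to support.

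**Conclusion.** The point holds in a limited form. The sole stated basis for 165 is the precision of a single proportion, which no objective or planned analysis targets and which this design could not estimate as a population prevalence. The calculation is correct, and the number may well be adequate. The defect is that the stated 95% confidence and 7-point margin do not carry over to the primary validation objective.

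As to size, an alpha observed at the 0.70 benchmark would be compatible with values from about 0.63 to 0.76, and children per item would lie between 5.5 and 13.75 for 30 down to 12 items. The alpha interval rests on Feldt's method and on all 165 children contributing complete item data. The children-per-item figures rest on assumed item counts.

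Severity: should-fix. The justification is unsuitable, but no enrolment figure or analysis has been shown to fail.

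**What to change.** 1. Keep 165. Remove the prevalence formula and the 7-point margin as the basis for the validation study.
2. State what 165 delivers for the planned analyses. For Cronbach's alpha, give the expected 95% confidence interval (about 0.63 to 0.76 at an observed 0.70), and report the estimate with its interval beside the 0.70 benchmark. The benchmark itself need not change.
3. For EFA, state the number of children per item once the fourth phase has fixed the item list. Until then, give it as a range over plausible item counts and do not treat 12 as final.
4. Reconcile the abstract's reference to randomized selection with the consent-based eligibility text, by describing the selection procedure or by removing the reference. The choice of sampling method is the investigators'.

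The cost is protocol wording and one additional interval in the report, with no extra participants. The downside is that the precision statement becomes less favorable than the present one and less simple to state.

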## Introduction

Down syndrome (DS) is the most common chromosomal anomaly [1], affecting approximately one in every 640 newborns [2]. It is characterized by the presence of an extra chromosome, which leads to atypical psychophysical development and associated disabilities. Individuals with DS often face numerous health complications due to multiple comorbidities, frequently requiring medical interventions, surgical procedures, and hospitalizations. As a result, they experience pain more often than their typically developing peers [3].

Children with DS are known to have a lower pain perception threshold [4], reduced pain tolerance, delayed reaction times, prolonged pain experiences, and altered nociceptive signal conduction and modulation [5,6]. Moreover, their expression of pain is often ambiguous and challenging to interpret, both qualitatively and quantitatively [7]. Verbal responses and crying may be minimal or absent, while facial expressions tend to remain evident [8,9], sometimes accompanied by immobility of the face and body. This response pattern, known as “freezing,” refers to a paralytic reaction that may give the false impression of pain insensitivity.

Recent studies focusing on facial expressions provide promising insights into understanding pain in this population. Careful observation of facial cues may help clinicians detect pain without being influenced by the patient’s cognitive abilities. Additionally, the pain experience in individuals with DS can vary greatly due to heterogeneous structural and functional alterations in the central nervous system, which affect the transduction, transmission, modulation, and perception of sensory information [10].

Pain recognition is further complicated by subtle or idiosyncratic behaviors and wide individual variability in physical and expressive abilities, which are closely tied to different levels of cognitive development. Although self-report remains the gold standard for pain assessment, it is often difficult to apply and interpret in individuals with intellectual disabilities [5]. Children with such disabilities face considerable disparities in pain-related care and remain significantly underrepresented in pain research. Standard pain assessment tools are frequently inadequate for this population, especially for those who are nonverbal or unable to understand and follow instructions [11].

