The ANDREAS tool will consist of observational items designed to capture specific behavioral indicators of pain in children with DS. Each item will follow a standardized structure and will be rated using a 5-point Likert scale (0 = never, 4 = always), based on either direct observation or caregiver report. Table 2 provides illustrative examples of item structure, behavioral domains, and the scoring criteria applied in the ANDREAS tool. The items will be organized into thematic domains such as facial expression, vocal behavior, and motor response. Their formulation will be grounded in qualitative findings derived from interviews and focus groups. To ensure consistent administration and interpretation, a coding manual containing operational definitions and detailed scoring guidelines will accompany the tool.

**Table 2 TAB2:** Examples of observational items included in the ANDREAS tool

Item example	Behavioral domain	Operational definition	Scoring scale
The child vocalizes through crying, moaning, or atypical sounds not attributable to known communicative patterns.	Vocal expression	Nonpurposeful vocalizations that occur in conjunction with observable signs of distress.	0 = never; 1 = rarely; 2 = sometimes; 3 = often; 4 = always
The child suddenly becomes immobile or assumes a rigid posture during a painful episode.	Motor behavior	A sudden cessation of voluntary movement lasting at least five seconds, not explained by external environmental stimuli.	0 = never; 1 = rarely; 2 = sometimes; 3 = often; 4 = always

Item development will follow an iterative, expert-led process involving multiple rounds of refinement, peer review, and pilot testing. This approach is intended to ensure that the tool remains closely aligned with the theoretical framework of pediatric pain in children with DS while also minimizing the risk of construct drift or item overfitting during the scale development process.

Training and standardization procedures

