Prior to data collection, all researchers and healthcare professionals responsible for administering the ANDREAS tool will participate in a standardized training program. This program will include theoretical instruction, practical simulations using case studies, and the review of annotated video recordings. Training will focus on ensuring consistent interpretation of items, accurate scoring, and reliable behavioral observation techniques. Inter-rater reliability will be evaluated during pilot testing by calculating agreement levels using Cohen’s kappa coefficient.

Behavioral coding protocol

Each behavioral indicator included in the ANDREAS tool will be operationally defined within a structured coding manual. This manual will outline detailed criteria for identifying and rating observable pain-related behaviors. For example, “freezing” will be defined as the sudden cessation of voluntary movement lasting at least five seconds, unrelated to any external stimulus. Depending on the item format, each behavior will be rated either using a binary presence/absence code or a 5-point Likert scale (0 = never, 4 = always). All data will be initially recorded on paper forms and then transcribed into a secure, GDPR-compliant digital platform for managing sensitive health information. Specific coding protocols will be uniformly applied across all cases to ensure the accuracy, reproducibility, and traceability of behavioral observations.

Statistical analysis

Descriptive statistics will be used to characterize the study population, including measures such as means, standard deviations, medians, interquartile ranges, proportions, and correlation coefficients. Summary tables will present key sociodemographic and clinical variables, including sex, age, pain localization, duration, and intensity, along with their respective ranges.

Psychometric validation of the ANDREAS instrument will proceed in multiple stages. Construct validity will be assessed through EFA, depending on data characteristics and sample size. Prior to EFA, the suitability of the dataset will be determined using the Kaiser-Meyer-Olkin measure of sampling adequacy, with a threshold of ≥ 0.60, and Bartlett’s test of sphericity, with statistical significance set at p < 0.05. Factor extraction will be based on eigenvalues greater than 1 and scree plot inspection, with factor loadings of ≥ 0.40 considered acceptable.

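### The coding-manual definition of freezing excludes any external stimulus, so read literally it codes freezing caused by the needle as absent and contradicts the abstract and the Table 2 item stem

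*Protocol article*

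**What the plan says.** The article describes or defines freezing in four places.

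- **Introduction.** Freezing is one of the ways in which children with Down syndrome express pain. It "refers to a paralytic reaction that may give the false impression of pain insensitivity".
- **Abstract, Results.** The indicator is introduced with the words "Key behavioral indicators, such as freezing" and is "defined as the absence of movement for at least five seconds during a painful stimulus".
- **Table 2 (Operationalization of the ANDREAS tool items).** The item stem reads "The child suddenly becomes immobile or assumes a rigid posture during a painful episode". The operational definition beside it reads "A sudden cessation of voluntary movement lasting at least five seconds, not explained by external environmental stimuli".
- **Behavioral coding protocol.** As its worked example of a manual definition, the section says freezing will be "the sudden cessation of voluntary movement lasting at least five seconds, unrelated to any external stimulus".

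The test setting is given under Inclusion Criteria: "Instrument testing will take place in healthcare facilities during venipuncture procedures". The Abstract's Methods paragraph lists "a standardized venipuncture protocol to induce pain" among the study components. The Behavioral coding protocol section adds that each behavior is scored either as present or absent or from 0 to 4, and that the same coding rules apply to every case.

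**The concern.** The manual is the text from which raters will score. Its definition has an exclusion with no exception for the painful procedure, and the painful procedure used to validate the tool is itself an external stimulus. A rater who follows the sentence as written must decide that immobility provoked by the needle is related to an external stimulus, and so score it absent, or 0.

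The behavior lost is the one the Introduction warns about: a child in pain who looks insensitive to it. A rule that scores this child as showing no freezing repeats, for that item, the error the tool is meant to correct. An item that misses the behavior it names also has less true signal to bring to the factor analysis and the reliability assessment.

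**Working it through.** No figure in the article bears on this point. The check is a comparison of wording against the test setting.

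**Step 1. The exclusion in each version.**

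| Place | Required link to pain | What is excluded |
|---|---|---|
| Abstract | Occurs during a painful stimulus | Nothing stated |
| Table 2, stem plus definition | Occurs in a painful episode | Immobility explained by the environment |
| Behavioral coding protocol | None in the definition | Immobility related to any external stimulus |

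**Step 2. Is the needle an external stimulus?** Yes. Venipuncture is applied to the child from outside, and the Abstract says that its purpose is to induce pain.

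**Step 3. Two test cases, each with an abrupt stop in voluntary movement lasting at least five seconds.**

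- *The child goes still because the needle enters.* The Abstract counts it. Table 2 counts it on its natural reading: the stem places the behavior in a painful episode, and the qualifier in the definition points to surroundings, not to the procedure. The coding protocol does not count it.
- *The child goes still because of a sudden noise before the needle.* The Abstract does not count it, since there is no painful stimulus yet. Table 2 does not, since the environment explains it. The coding protocol does not.

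The versions agree on the distractor and part on the case of interest. Taken literally, the coding protocol keeps only freezing that nothing external provoked, which in a venipuncture study leaves out the response being studied.

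**Step 4. Bounds on the effect.** Let *f* be the proportion of children who freeze because of the needle, and *q* the proportion of those cases scored by the literal rule. Recorded needle-evoked freezing is then *f*(1 − *q*). With *q* = 0 it is *f*, and nothing is lost. With *q* = 1 it is 0, and all of it is lost. The article gives neither *f* nor *q*, so only the direction (undercounting) and these limits can be stated.

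**The case against.** The strongest reply is that the intent is plain. The sentence before the definition says that the manual covers pain-related behaviors, the Introduction treats freezing as a response to pain, and Table 2 has the narrower qualifier that the coding protocol seems to have dropped. The manual is still to be written, items will go through refinement, peer review and pilot testing, and raters will be trained with annotated videos. A sensible trainer would probably not teach that a freeze at needle entry does not count.

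This stands as evidence of what the authors meant, and it limits the severity. It does not cure the text. The article states the definition positively, offers it as the example of how the manual will work, and promises uniform application. Nor is this a matter of condensation: nothing is missing, but what is stated conflicts with other parts of the article.

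A reader might infer more than the documents support:

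- *That there are three mutually incompatible definitions.* Table 2, read with its stem, is compatible with the Abstract. The conflict lies in the coding protocol's phrase.
- *That the tool's central item is defeated.* Freezing is given as one example of the key indicators, and the item list is finalized only in the fourth phase.
- *That the item will have almost no variance and drop out of the factor analysis, or that kappa will suffer.* Neither is derivable. The first needs every rater to apply the literal rule, the second needs raters to differ, and both cannot hold in full together. One manual and common training also make the second less likely. Some items may be scored from caregiver report, which neither account considers.
- *That the Abstract's wording would count children who are held or told to keep still.* The article describes neither holding nor such an instruction.

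**Conclusion.** The contradiction is real and sits in one phrase of the Behavioral coding protocol section. As written, it excludes needle-evoked freezing from an indicator that the Abstract and the Table 2 stem tie to pain. The consequence is an undercount of one named key indicator and a weaker freezing item in the validation. The loss lies between none and all needle-evoked freezing, depending on how raters read the phrase.

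The conclusion assumes only that venipuncture is an external stimulus and that the manual will carry the definition the article prescribes for it. The correction should be made before data collection, as a should-fix point. It does not show that the instrument or its validation fails.

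**What to change.** Delete the exclusion of any external stimulus and use one definition in the Abstract, Table 2 and the coding manual, with three elements:

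1. an abrupt stop in voluntary movement that lasts five seconds or more;
2. occurrence during a painful episode or stimulus;
3. no explanation by a non-painful event in the surroundings, with an explicit statement that the painful procedure itself is not an excluded stimulus.

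The definition should not be tied to a time window around venipuncture. Items may be scored from caregiver report, the Results and Conclusions sections foresee use at home as well as in the clinic, and the Introduction reports delayed reactions in these children. A window could miss late freezing and would bind a general pain item to one procedure.

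The cost is a sentence in three places and matching training material. It should be done before scoring starts, because freezing scored as absent on a paper form may not be recoverable afterwards.
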